### 2.5. Data Analysis

#### 2.5.1. Quantitative Analysis

Statistical analysis will be performed using IBM SPSS Statistics, version 27.0 (IBM Corp., Armonk, NY, USA). For categorical variables, absolute frequencies and percentages will be calculated. For quantitative variables, means and standard deviations (SDs) or medians and interquartile ranges will be reported, depending on whether the variables follow a normal distribution. This study has a single confirmatory primary analysis: the baseline-adjusted between-group difference in the EQ-5D index at 1 month, evaluated at a two-sided α level of 0.05. The EQ-5D contrast at 4 months and the prespecified secondary outcomes will be treated as supportive secondary analyses. Analyses of ad hoc outcomes, treatment-effect modification, subgroup analyses, per-protocol analyses, and the month-seven maintenance assessment will be considered exploratory. No global formal adjustment for multiplicity will be applied to these secondary and exploratory analyses because they will not be used to support independent confirmatory claims. Effect estimates and 95% confidence intervals will be emphasized; *p* values for secondary and exploratory analyses will be reported as nominal and interpreted cautiously in the context of multiple testing, and isolated nominal *p* values < 0.05 will not be considered confirmatory evidence.

Continuous secondary outcomes measured repeatedly will be analyzed using analogous linear mixed-effects models. Binary outcomes will be analyzed using logistic generalized linear mixed-effects models; count outcomes will be analyzed using Poisson or negative-binomial mixed-effects models, according to dispersion; and ordinal outcomes will be analyzed using an appropriate ordinal mixed-effects model when applicable.

The primary analysis will follow the intention-to-treat principle. All of the randomized participants will be analyzed in the group to which they were originally assigned, regardless of their adherence to the intervention. The participants attending fewer than four workshop sessions will be classified as non-adherent, but will not be considered lost to follow-up and, unless they withdraw consent, will continue to be invited to complete the scheduled outcome assessments and will remain included in the intention-to-treat population. Intervention discontinuation, adherence, and loss to outcome follow-up will be recorded separately. Longitudinal mixed-effects models will use all available outcome measurements and will be estimated by maximum likelihood under a missing-at-random assumption. Intervention discontinuation, adherence, and loss to outcome follow-up will be recorded separately. If outcome data are missing, multiple imputation under a missing-at-random assumption will be used as a prespecified sensitivity analysis, including treatment allocation, baseline outcome values, available repeated outcome measurements, relevant baseline prognostic variables, and available information related to attendance/adherence and missingness.

When sample size allows, quantitative results will be described, disaggregated by sex, and potential differences in primary and secondary variables will be explored. Sex will be included as a prespecified exploratory effect modifier. For longitudinal outcomes, the treatment × sex and treatment × visit × sex interactions will be assessed. Where the data permit, adjusted intervention effects will be presented separately by sex, with 95% confidence intervals. These analyses will be considered exploratory, as this study was not specifically powered to detect interaction effects.

Given that the participants in the intervention arm receive the intervention in workshop groups, and that all workshop sessions are conducted at the same study center using the same structure and standardized procedures, a workshop-level random effect will be considered within the intervention arm to account for potential residual correlation and heterogeneity across workshop sessions. The structure is partially nested, as the participants in the control group are not assigned to workshops.

The participants who do not complete the 4-month questionnaires will be considered lost to follow-up. Their sociodemographic and clinical characteristics, as well as their baseline scale scores (included in the baseline assessment), will be analyzed to characterize the profile of these patients. If, during follow-up, a participant from either the control or intervention group modifies their medication or the therapies they receive, they will not be considered lost to follow-up; they will remain in this study, and changes will be assessed at 1, 4, and 7 months. The patients originally assigned to the control group will not be included as part of the intervention group in this study. Although they will be offered the opportunity to participate in a workshop after completing their follow-up as controls, they will not be considered part of the intervention group for study purposes.

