### 2.3. Data

#### 2.3.1. Outcomes

The primary outcome will be the between-group difference in health-related quality of life (QoL), assessed using the EuroQol-5D (EQ-5D) index score [27] at one month, adjusted for baseline values, and reported with its 95% confidence interval. Intervention effectiveness will be evaluated primarily on the basis of this randomized between-group comparison. Improvements greater than 0.10 in the EQ-5D index will be used to aid interpretation of the magnitude of the estimated treatment effect and will not constitute a separate criterion for declaring effectiveness.

The EQ-5D index will also be assessed at 4 months in both randomized groups as a supportive secondary assessment. The additional month-seven assessment in the intervention group will be considered an exploratory evaluation of the maintenance of effect and will not be used for randomized between-group inference because the control group will be offered the workshop after the 4-month comparative period.

Secondary outcomes will include pain intensity, pain catastrophizing, subjective well-being, self-esteem, mood, resilience, anxiety and depression, medication use, health habit improvement, and healthcare resource use. The participant experience-related outcomes will include satisfaction, perceived usefulness of the techniques learned, recommendation of the workshop, perceived impact on daily life, and suggestions for improvement.

The planned outcomes and measurement instruments are summarized in Table 1. The use of validated scales and ad hoc patient-reported outcome and experience measures in previous evaluations of the workshop is described elsewhere [22,23].

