#### 2.3.4. Data Management

The study data will be managed using the MoviSalud RPM (Remote Patient Monitoring) platform, adapted for this project. The platform will centralize data entered by the participants through the mobile app and will allow the research team to access these data through a professional web portal.

An internal medicine physician from the research team will conduct recruitment through a telephone interview to verify whether the patient meets the inclusion criteria. If eligible, the physician will inform the patient about this study and the possibility of being allocated to either the intervention or the control group and will obtain informed consent. Once a cohort of 40 patients has been recruited, the physician will notify the research support technician, who will register and enroll them in the app.

Once enrolled in the platform, the patient will have access exclusively to the baseline assessment forms prior to randomization. Once patients have completed the baseline assessment, randomization will be requested. Treatment allocation cannot be predicted in advance.

Allocation to the study arm will be performed automatically by the system through an atomic and irreversible transaction, with a timestamp and audit trail; no individual will be involved in the allocation process. The recruitment wave will then be closed, the corresponding workshop cohort will be established, and the control group will be activated. Within each combination of recruitment wave and stratum, permuted blocks of size 4 or 6 will be generated, with the block size selected randomly and independently for each block, with a probability of 0.50 for each size. With recruitment waves of approximately 40 participants divided into two sex strata, and considering the higher expected prevalence of women among individuals with chronic pain, the male stratum may comprise approximately 10–12 participants per wave. Blocks of size 8 would, therefore, result in a relatively high number of incomplete blocks at the end of each recruitment wave, which would be contrary to the intended purpose of blocking. Block sizes of 4 and 6 limit the maximum imbalance within each stratum to three participants, while preserving allocation unpredictability.

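### Allocation is blocked by recruitment wave and sex, but the primary model as described adjusts for baseline EQ-5D alone, so its intervention-only workshop effect absorbs shared wave variation and overstates the standard error

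*Protocol article*

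**What the plan says.** **Randomization (section 2.3.4).** "Within each combination of recruitment wave and stratum, permuted blocks of size 4 or 6 will be generated". The strata are defined by sex: "With recruitment waves of approximately 40 participants divided into two sex strata", of whom "the male stratum may comprise approximately 10–12 participants per wave". After allocation, "The recruitment wave will then be closed, the corresponding workshop cohort will be established, and the control group will be activated". Read plainly, each wave gives one workshop and one set of concurrent controls.

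**Primary analysis (sections 2.3.1 and 2.5.1).** The only confirmatory analysis is "the baseline-adjusted between-group difference in the EQ-5D index at 1 month", tested at a two-sided alpha of 0.05. The outcome definition says the difference is "adjusted for baseline values, and reported with its 95% confidence interval".

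**Other model terms (section 2.5.1).** Sex enters as an exploratory effect modifier. A workshop random effect is to be considered within the intervention arm, with this reason: "The structure is partially nested, as the participants in the control group are not assigned to workshops". Section 2.2.1 calls that model prespecified, and the Limitations say it will address the dependence. Estimation is by maximum likelihood. Recruitment wave is not mentioned in the analysis section.

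**The concern.** In the intervention arm, wave and workshop are the same grouping. Anything that shifts a whole wave (season, referral mix) moves the workshop participants and their concurrent controls together. Because allocation is balanced within waves, that shift drops out of the treatment difference.

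A model with a random effect in the intervention arm only cannot see this. It reads the wave shift among intervention participants as a workshop effect, adds it to the variance of the treatment difference, and ignores the matching similarity among same-wave controls. The stated reason for the structure, that controls belong to no workshop, is true, but controls do belong to waves.

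At stake is the precision of the trial's one confirmatory test: an interval that is too wide and power below the planned 80%.

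**Working it through.** **1. The plan's own figure.** Two-sample t-test, d = 0.50, two-sided alpha 0.05, power 0.80, 1:1 allocation: 63.77, so 64 per arm, 128 in total, with power 0.801. After 20% loss, 128/0.80 = 160. Both reproduce. At about 40 per wave, 160 is 4 waves and the target of 180 is 4.5.

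**2. Inputs.** From the article: d = 0.50, SD 0.197, 64 analysed per arm, about 40 per wave, 10 to 12 men in 40. Assumed, because the article gives no intraclass correlation: the share s of residual variance lying between waves (0 to 10%), and no true workshop effect. Residual variance after baseline adjustment is set to 1.

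**3. Closed form.** With k waves and n analysed per arm, the variance of the treatment difference is:

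- true, and with wave in the model: 2(1 − s)/n
- as reported by the intervention-only model: s/k + (1 − s)/n + 1/n

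At s = 5%, k = 4, n = 64:

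- with wave: 2 × 0.95/64 = 0.02969, SE 0.1723
- without: 0.0125 + 0.01484 + 0.01563 = 0.04297, SE 0.2073

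Power is Φ(0.50/SE − 1.96).

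| Wave share | SE overstated by | Power without wave | Power with wave |
|---|---|---|---|
| 0 | 0% | 80.7% | 80.7% |
| 1% | 4% | 77.9% | 81.1% |
| 2% | 8% | 75.1% | 81.5% |
| 5% | 20% | 67.4% | 82.7% |
| 10% | 39% | 57.1% | 84.6% |

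This is an upper guide, because it charges the whole wave variance to workshops.

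**4. Simulation under the plan's estimator.** Maximum likelihood, 4 waves of 16 per arm, 2,500 trials per setting, normal critical values. Here the comparison model has wave as fixed effects.

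| Wave share | Sampling SD | Mean SE without / with | Estimated workshop variance (true 0) without / with | Power without / with |
|---|---|---|---|---|
| 0 | 0.173 | 0.180 / 0.176 | 0.009 / 0.005 | 80.7% / 82.3% |
| 2% | 0.176 | 0.185 / 0.175 | 0.019 / 0.006 | 78.0% / 81.7% |
| 5% | 0.173 | 0.193 / 0.171 | 0.035 / 0.004 | 75.0% / 83.2% |
| 10% | 0.167 | 0.209 / 0.167 | 0.067 / 0.005 | 68.3% / 84.6% |

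Maximum likelihood picks up only part of the wave variance (0.035 of 0.05), so the SE excess at 5% is about 12% (0.193/0.1723 = 1.12) rather than 20%. In EQ-5D units that is 0.193 × 0.197 = 0.038 against 0.1723 × 0.197 = 0.034, or a 95% half-width of about 0.075 against 0.067. Type I error without wave at 5% was 3.5% (1,000 trials).

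The 1.6 points at zero share (82.3 − 80.7) go with a smaller estimated workshop variance in the fixed-wave fit, although there is no wave variance to remove. They are not real information, and part of the other differences in the last column has the same source.

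**5. Wave as a shared random intercept, maximum likelihood.** At 5%, power was 74% without and 79% with it; with Satterthwaite degrees of freedom (800 trials), 68% and 76%. At 2% the gain was about 2 points. With step 4, this gives the range of 5 to 8 points at 5% and 2 to 4 at 2%.

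**6. If no workshop term is fitted.** The SE ratio is 1/√(1 − s): +1.0% at 2% and +2.6% at 5%.

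**7. Sex alone.** Its variance share is p(1 − p)δ², with p = 0.25 to 0.30 and δ the assumed sex difference in SD. For δ = 0.2 the share is 0.0075 to 0.0084 and the SE rises by about 0.4%. For δ = 0.5 the share is 0.047 to 0.053 and the SE rises by 2.4 to 2.7%.

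**The case against.** **The covariate list may stand elsewhere.** A reader might infer that the plan excludes the stratification factors. The text does not say so. It names baseline values and is silent on the rest, and a condensed article may leave the full list to a protocol or analysis plan not shown. This stands as a limit on the wording. It does not remove the point: the article does fix a random-effect structure, gives its reason, and assigns sex a role, and that structure mis-states the standard error under the randomization described.

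**The wave variance may be small.** There is one centre, one team with fixed materials, one set of entry criteria and 12 months of recruitment, and baseline EQ-5D will take up some case-mix. This stands. At shares of 1 to 2% the gain is 2 to 3 points, and about 1.5 points if true workshop variance is 0.05. With 180 recruited (5 waves, 72 analysed per arm), the closed form still gives 80.4% power without wave at a 2% share, against 85.8% with it. At 5% it gives 73.8% against 86.8%.

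**Much lower power figures can be produced.** With REML and Satterthwaite-type degrees of freedom, the model without wave has 58% power at a 5% share. A reader might put all of the shortfall from 80% down to the missing wave term. That would be wrong: the same analysis has 70% power at zero wave variance with or without the term. That part comes from estimating workshop variance from four groups, and the plan's estimator is maximum likelihood.

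**The workshop effect is only to be considered.** True of section 2.5.1, and without it the loss is 1.0 to 2.6% in SE. But section 2.2.1 calls the model prespecified and the Limitations rely on it.

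**Conclusion.** The point holds as a loss of reported precision. If the intervention-only workshop effect is fitted without wave, the standard error is overstated and the test is conservative. Under maximum likelihood with 4 waves, 64 analysed per arm and no true workshop effect, the cost is roughly 5 to 8 points of power at an assumed 5% wave share, about 2 to 4 points at 2%, and none at zero. Sex contributes little beyond consistency with the design.

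A reader might also infer bias or a risk of false positives from omitting the strata. Neither follows here: the estimate is unbiased, and type I error without wave was about 3.4 to 3.5% at a 5% share, below the nominal level.

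The figures rest on assumed wave shares, on one workshop per wave, and on residual variance as it stands after baseline adjustment. The change is worth making because it is cheap and aligns the analysis with the groups used for randomization, not because a large loss has been shown.

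**What to change.** In the primary model and the analogous secondary models, include sex as a fixed effect and recruitment wave as a random intercept shared by both arms, next to baseline EQ-5D and the intervention-arm workshop effect. Estimate by REML with a named small-sample degrees-of-freedom method, such as Satterthwaite or Kenward-Roger.

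The degrees-of-freedom method is part of the fix. Under maximum likelihood with wave in the model, type I error reached about 7 to 8% at a 2% wave share with a true workshop variance of 0.02.

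**Cost.** Two sentences of analysis text, one more fixed effect, and one more variance parameter estimated from only 4 or 5 waves. The randomization system already holds both variables. If wave variance is near zero there is little or no gain: under REML with Satterthwaite-type degrees of freedom, power is 70% with or without the shared intercept at zero share, 58% against 64% at 5%, and 45% against 61% at 10%. The move from maximum likelihood to REML with small-sample degrees of freedom itself lowers power on paper. That is the price of controlling type I error with so few workshops, and should be accepted knowingly.

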#### 2.1.3. Intervention

The participants allocated to the intervention group will receive a multicomponent psychoeducational workshop focused on self-management, pain control, and emotional regulation, based on NPhTs.

The participants will continue to receive their usual healthcare. Participation in the workshop will not require discontinuation or mandatory modification of analgesic medication, psychotropic drugs, or any other usual treatments. Any reduction, withdrawal, or modification of pharmacological treatment will occur, where applicable, at the patient’s decision and/or according to the judgement of the healthcare professionals responsible for their usual clinical care. Current pharmacological treatment will be recorded both at baseline and at the different follow-up time points (months 1, 4, and 7, with the latter only in the intervention group), as well as whether the participants are receiving physiotherapy, psychological treatment, or complementary therapies (specifying which ones); whether they engage in regular physical exercise (specifying the type and frequency); whether they are currently receiving care from a pain management unit; and whether they use healthcare services due to pain (emergency department visits, scheduled outpatient visits, and hospitalizations). This information will allow us to document changes in the healthcare received over the course of this study.

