For interpretative purposes, previously reported clinically relevant change thresholds will be considered where available: approximately 0.03–0.10 for the EQ-5D index and ≥7–10 points for the EQ-5D visual analogue scale [34,35]; ≥2 points for pain intensity [36]; 2–3 points for self-esteem [37]; 1.5–1.7 points per HADS subscale [38,39]; and approximately 9–11 points for pain catastrophizing [40]. For the well-being and resilience scales, no established and validated minimal clinically important difference (MCID) has been identified. Therefore, in these cases, the effect size of the observed changes will be assessed. The results derived from the ad hoc questionnaires, including questions on mood, health habits, self-perceived improvement in self-esteem, satisfaction measures, and questions regarding perceived impact (effectiveness of the techniques and changes in medication), will be considered exploratory measures, as they are not based on validated scales.

All of the patients (control and intervention groups) will record the following information on the baseline data collection form: medication name, dose, frequency of administration, and rescue medication (if pain is not relieved). They will provide this information again at 1 and 4 months. Based on the information reported by patients at baseline and during follow-up, the number of analgesics and anxiolytics/antidepressants/hypnotics will be recorded at baseline and at each follow-up assessment.

Participant experience-related outcomes will be assessed at the end of the workshop. These will include overall satisfaction, perceived usefulness of the techniques learned, recommendation of the workshop, the techniques considered most useful, and perceptions of the impact of the intervention on pain, health habit improvement, mood, self-esteem and life project, and they will provide a self-assessment of changes in medication (whether there was a reduction in the frequency or dose of analgesics/psychotropic medications, whether they switched to a lower-level medication, or whether they discontinued one or more medications).

Suggestions for improvement and free-text comments will also be collected. These aspects will be assessed using ad hoc questionnaires and semi-structured interviews.

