## Figures and Tables

**Table 1 healthcare-14-03063-t001:** Planned outcomes and measurement instruments.

Outcome/Domain	Measurement Instrument or Indicator
Health-related QoL	EuroQol-5D (EQ-5D): index value and visual analogue scale [27]
Pain intensity	0–10 numeric pain rating scale [28]
Subjective well-being	0–10 numeric well-being scale developed within the program [22,23]
Self-esteem	Spanish version of the Rosenberg Self-Esteem Scale [29]
Resilience	Spanish version of the Brief Resilience Scale (BRS) [30,31]
Anxiety and depressive symptoms	Spanish version of the Hospital Anxiety and Depression Scale (HADS) [32]
Pain catastrophizing	Spanish version of the Pain Catastrophizing Scale (PCS) [33]
Mood	Ad hoc categorical item: cheerful, normal, discouraged, or depressed [22,23]
Medication use	Number of medications and changes in analgesic regimen [22,23]
Health habits	Ad hoc items on self-reported habit improvement [22,23]
Healthcare resource use	Number of emergency department visits and scheduled consultations related to CP or to exacerbation or complications of the underlying condition causing pain
Participant experience	Ad hoc questionnaires and semi-structured interviews

**Table 2 healthcare-14-03063-t002:** Participant timeline and study procedures.

Timepoint/Period	Timing	Participants Involved	Main Procedures
Screening/inclusion	Before baseline	Potentially eligible patients	Eligibility assessment; participant information; informed consent
T0: Baseline	Month 0	Both groups	Randomization; collection of sociodemographic and clinical variables; outcomes assessment (1)
Intervention period	Month 0–1	Intervention group	Workshop sessions
T1: End of workshop	Month 1	Both groups	Outcomes assessment (2)
		Intervention group	Workshop satisfaction and perceived impact
Qualitative follow-up	Month 2–3	Intervention group	In-depth semi-structured interviews (3)
T2: Follow-up	Month 4	Both groups	Outcomes assessment (2)
		Control group	Offer of the workshop
T3: Follow-up	Month 7	Intervention group	Outcomes maintenance assessment (2)

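### Poisson and negative-binomial mixed models give intervals that are too wide for medication counts if drug lists are fairly stable within a person

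*Protocol article*

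**What the plan says.** Section 2.3.1 lists medication use among the secondary outcomes, and Table 1 measures it as "Number of medications and changes in analgesic regimen". Section 2.3.1 adds that "the number of analgesics and anxiolytics/antidepressants/hypnotics will be recorded at baseline and at each follow-up assessment". For both arms it says "They will provide this information again at 1 and 4 months", so the randomized comparison uses three counts per person.

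Section 2.5.1 states the model family: "count outcomes will be analyzed using Poisson or negative-binomial mixed-effects models, according to dispersion". It names no other model for a count. The longitudinal mixed models "will be estimated by maximum likelihood under a missing-at-random assumption". The section mentions no robust variance, free scale parameter or option for counts that vary less than Poisson counts. On the role of the result, it says that "the prespecified secondary outcomes will be treated as supportive secondary analyses", with effect estimates and 95% confidence intervals given the emphasis.

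**The concern.** Given the random intercept, a Poisson model sets a person's visit-to-visit variance equal to that person's mean. A negative-binomial model can only add to it. Someone taking three drugs is therefore modelled as varying around three with a variance of at least 3. Choosing between the two models by dispersion covers excess variance only.

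Emergency visits and consultations are new events in each period, so these models are a natural choice for them. The number of drugs in use is a running stock: at months 1 and 4 largely the same items are counted again, and within-person variance may be a small fraction of the mean. Overdispersion between people does not help, because the misfit is within the person.

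The intervals that the plan means to emphasize would then be too wide, and a modest real reduction could be reported as no evidence of an effect. Section 1.1 says that earlier non-randomized evaluations suggested improvement in medication use, so readers will look at this outcome.

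**Working it through.** **Inputs from the protocol.** Section 2.2.1 gives 64 per arm before allowance for loss. That figure reproduces: a two-sided t-test with d = 0.50, α = 0.05 and power 0.80 needs 63.8, so 64 per arm, and 128/0.80 = 160. It concerns the EQ-5D index; no power is stated for medication counts. The α ("evaluated at a two-sided α level of 0.05") is set for the primary analysis and is used here for nominal tests.

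**Assumed, because the protocol gives no mean, spread or rate of change for drug counts.** A mean of 2.5 or 3 drugs; baseline counts under-, equi- and over-dispersed between people; stopping rates as shown; 64 per arm analysed; no workshop random effect.

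**Analytic check.** With arm, visit and arm-by-visit terms, the baseline-to-month-4 contrast combines four cell totals, each with expected count n × mean. The model therefore gives SE(log rate ratio) = sqrt(4/(n × mean)).

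- Mean 3: sqrt(4/192) = 0.144. Around a ratio of 1 the interval is exp(±1.96 × 0.144), about 0.75 to 1.33.
- Mean 2.5: sqrt(4/160) = 0.158, giving about 0.73 to 1.36.

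The stability of the lists does not enter this formula. Under this coding a reduction of about 25% must be observed to exclude no effect.

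**Simulation A.** Mean 3, each person dropping at most one drug per interval, 300 trials per scenario, maximum-likelihood Poisson random-intercept model. Ranges run over the three baseline distributions. In the three coding columns the first entry is model SE divided by actual sampling SD, and the second is the share of trials that reject. The ANCOVA column gives the share that reject.

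| Chance of dropping a drug, control / intervention | Lists unchanged at month 4 | Arm × visit | Common baseline | Log-baseline covariate | ANCOVA on the count |
|---|---|---|---|---|---|
| 5% / 5% (no effect) | 85–87% | 5.8–6.4; 0% | 1.7–2.2; 0–0.7% | 3.4–4.4; 0% | 4.7–7.3% |
| 5% / 20% | 73–76% | 4.1–4.4; 0% | 1.6–2.0; 0.3–3.3% | 2.8–3.1; 0–0.3% | 86–92% |
| 10% / 25% | 63–68% | 3.5–3.9; 0% | 1.5–2.0; 0.7–4.3% | 2.5–2.6; 0–1.3% | 76–80% |
| 10% / 40% | 51–56% | 2.8–3.0; 3–16% | 1.5–1.8; 24–51% | 2.1–2.2; 43–71% | 99–100% |
| 5% / 50% | 55–61% | 2.8–3.0; 50–91% | 1.4–1.7; 73–90% | 2.2–2.3; 96–100% | 100% |

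Rows 2 and 3 are reductions of about 9% to 11% (for example 1 − 2.67/2.95 = 9.5%), row 4 about 20% (1 − 2.35/2.97 = 21%), and row 5 about 27% to 30% (1 − 2.08/2.95 = 29.5%). The 0% in row 2 follows from the inputs. With under-dispersed counts the mean estimate is −0.110, the model SE 0.147 and the actual SD 0.036. Significance needs 1.96 × 0.147 = 0.288, which lies (0.288 − 0.110)/0.036 = 4.9 SDs away.

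**Simulation B.** Mean 2.5, each drug stopped independently with some new starts, common baseline coding. Two separately programmed runs are combined except where noted.

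- 5% to 15% stopped in both arms: SE ratio 1.4 to 2.2; the null is rejected in 0% to 2% of trials.
- 40% turnover: SE ratio about 1.2 to 1.6.
- 15% versus 5% stopped (before new starts, 1 − 0.85/0.95 = 10.5%): power 1% to 4%, against 62% to 70% for a baseline-adjusted model with robust SE.
- 25% versus 15% stopped (one run): 2% to 7%, against 31% to 36%.
- 25% versus 5% stopped: 19% to 37%.
- 35% versus 5% stopped (before new starts, 1 − 0.65/0.95 = 31.6%): about 80%.

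**Is a robust SE enough?** In a further run with mean 3 and 5% versus 20% dropped, the common-baseline mixed model had 7.5% power with its own SE and 33% with a sandwich SE. ANCOVA and Poisson with a log-baseline covariate and sandwich SE both had 95%. The baseline adjustment matters as well as the variance.

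**The case against.** **Stability is assumed.** The protocol gives no turnover figure. Section 2.1.3 says that "Participation in the workshop will not require discontinuation or mandatory modification of analgesic medication, psychotropic drugs, or any other usual treatments", but it also leaves reduction or withdrawal open to the patient and the treating professionals. This stands: the size is conditional. Reporting error in app entries would also add within-person noise. With an assumed 15% of omissions and additions, the SE ratio falls to 1.3–1.4, and power for 25% versus 5% stopped is 21–25%, against 51–60% for ANCOVA. The loss shrinks but does not vanish.

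**The details belong in the analysis plan.** How baseline enters and which variance estimator is used may be settled in a document not shown, and the article does not exclude robust variance. That limits any firm multiplier. It does not remove the point, because the article itself states the model family and maximum likelihood, and its only stated choice runs the wrong way for stable counts.

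**Medication use is more than this count.** Table 1 also lists regimen changes, which could go to the binary or ordinal models. Section 2.3.1 treats the self-assessed medication changes as exploratory. Neither repairs the interval for the count.

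**The stakes are limited.** The error is conservative, and secondary p values are nominal. This stands.

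**A stronger reading is tempting:** that the trial would almost never detect a medication effect, whatever happened. The documents do not support it. They give no counts from which it could follow, and in the simulations large reductions are mostly detected.

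**Conclusion.** The point holds in conditional form. The stated models cannot represent within-person variance below the mean, so the 95% confidence intervals for medication counts are too wide if drug lists are fairly stable between visits. Under the assumptions above, the standard error is about 1.4 to 2.2 times too large with a common baseline, up to about 6 times with arm-by-visit coding, and about 1.2 to 1.6 times at 40% turnover. Reductions near 10% would be found in a few percent of trials. A baseline-adjusted robust analysis would find about 60% to 70% when 15% rather than 5% of drugs are stopped, and fewer when background turnover is higher. At about 20% reduction the planned power is anywhere from 3% to 71%, depending on coding; from about 25% to 30% upward most effects are still detected.

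The negative-binomial version was not simulated, but it can only add variance. The harm is an uninformative interval, and possibly a mistaken reading of no effect, on one supportive secondary outcome. The primary EQ-5D conclusion is unaffected. Emergency visits and consultations were not tested and are not criticised here.

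**What to change.** In Section 2.5.1, take the number of analgesics and the number of anxiolytics, antidepressants and hypnotics out of the count-model sentence. State that they will be analysed with the baseline-adjusted linear mixed model used for continuous outcomes, with robust standard errors. Poisson regression adjusted for the baseline count, with person-clustered robust variance, is an alternative. Keep the Poisson and negative-binomial mixed models for emergency visits and consultations.

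In simulation A, ANCOVA and the baseline-adjusted Poisson model with sandwich SE rejected a true null in about 4% to 8% of trials. The cost is one sentence of analysis wording. With the linear model the effect becomes a difference in mean number of drugs instead of a rate ratio; the Poisson alternative keeps the ratio.
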